## Abstract

**Background:**

The decline in skeletal muscle mass experienced following a short-term period (days to weeks) of muscle disuse is mediated by impaired rates of muscle protein synthesis (MPS). Previous RCTs of exercise or nutrition prehabilitation interventions designed to mitigate disuse-induced muscle atrophy have reported limited efficacy. Hence, the aim of this study is to investigate the impact of a *complex* prehabilitation intervention that combines β-lactoglobulin (a novel milk protein with a high leucine content) supplementation with resistance exercise training on disuse-induced changes in free-living integrated rates of MPS in healthy, young adults.

**Methods/design:**

To address this aim, we will recruit 24 healthy young (18–45 years) males and females to conduct a parallel, double-blind, 2-arm, randomised placebo-controlled trial. The intervention group will combine a 7-day structured resistance exercise training programme with thrice daily dietary supplementation with 23 g of β-lactoglobulin. The placebo group will combine the same training programme with an energy-matched carbohydrate (dextrose) control. The study protocol will last 16 days for each participant. Day 1 will be a familiarisation session and days 2–4 will be the baseline period. Days 5–11 represent the ‘prehabilitation period’ whereby participants will combine resistance training with their assigned dietary supplementation regimen. Days 12–16 represent the muscle disuse-induced ‘immobilisation period’ whereby participants will have a single leg immobilised in a brace and continue their assigned dietary supplementation regimen only (i.e. no resistance training). The primary endpoint of this study is the measurement of free-living integrated rates of MPS using deuterium oxide tracer methodology. Measurements of MPS will be calculated at baseline, over the 7-day prehabilitation period and over the 5-day immobilisation period separately. Secondary endpoints include measurements of muscle mass and strength that will be collected on days 4 (baseline), 11 (end of prehabilitation) and 16 (end of immobilisation).

**Discussion:**

This novel study will establish the impact of a bimodal prehabilitation strategy that combines ß-lactoglobulin supplementation and resistance exercise training in modulating MPS following a short-term period of muscle disuse. If successful, this complex intervention may be translated to clinical practice with application to patients scheduled to undergo, for example, hip or knee replacement surgery.

**Trial registration:**

NCT05496452. Registered on August 10, 2022.

Protocol version: 16-12-2022/1

**Supplementary Information:**

The online version contains supplementary material available at 10.1186/s13063-023-07329-6.

## Background

The term *muscle disuse* refers to a scenario in which a muscle group(s) is unloaded over an extended (> 2 days) time period, e.g. limb immobilisation due to injury or following surgery. A period of limb immobilisation-induced muscle disuse is widely established to cause muscle atrophy [8]. In this regard, only 5 days of leg immobilisation was sufficient to elicit a physiologically relevant (3.5%) decline in quadriceps muscle CSA [32]. At the metabolic level, this muscle atrophy is primarily mediated by a decreased response of muscle protein synthesis (MPS) rather than increased stimulation of muscle protein breakdown [24]. Accordingly, a study by the same group demonstrated an ~ 30% decline in response of MPS to protein ingestion after 14 days in a leg brace, indicating that immobilisation led to a state of muscle anabolic resistance [33]. These findings highlight the importance of targeted, non-pharmacological, interventions to attenuate the immobilisation-induced decline in MPS in order to maintain muscle mass during unplanned (i.e. injury) or planned (i.e. surgery) periods of disuse.

Resistance exercise training serves as the most potent non-pharmacological stimulus of MPS [4]. Moreover, the provision of dietary amino acids in combination with resistance exercise exhibits an additive effect, stimulating MPS to a greater degree than exercise alone [5]. Multiple clinical trials have investigated the efficacy of a nutritional intervention to mitigate the suppressed response of MPS during a period of immobilisation [34], However, to our knowledge, no studies to date have investigated the impact of a combined nutritional and exercise prehabilitation programme, implemented prior to a period of immobilisation, on mitigating the disuse-induced decline in MPS and muscle mass. To fill this gap in knowledge, we will conduct a placebo-controlled clinical trial that combines β-lactoglobulin supplementation as a novel milk protein with resistance exercise training and measure integrated free-living rates of MPS before and after 5 days of limb immobilisation. The placebo group will be an energy-matched carbohydrate (dextrose) control.

The biological rationale for administering β-lactoglobulin supplementation in the present study is underpinned by two primary lines of evidence. First, β-lactoglobulin exhibits an exceptionally high leucine content (16%) that exceeds the constituent leucine profile (~ 12%) of whey protein [21]. In addition to providing substrate for the synthesis of new muscle protein, leucine also acts a signalling molecule to trigger MPS via activation of the mechanistic target of rapamycin complex 1 (mTORC1) pathway [1, 2]. Accordingly, several studies have reported a greater acute response of MPS to ingestion of a leucine-rich intact whey protein bolus vs. a dose-matched soy or casein protein bolus that exhibits a lower leucine content [9, 29]. Notwithstanding, it is plausible that a ‘ceiling effect’ may exist regarding leucine availability and the postprandial stimulation of MPS, as evidenced by our previous observation of a plateau in the dose–response of MPS to ingested whey protein in healthy young men [36]. Although a strong positive correlation (*r* = 0.66) between peak plasma leucine concentrations (manipulated by ingestion of intact whey or casein protein) and postprandial rates of MPS rates has been reported in a relatively larger cohort (*n* = 48) of older men [23], this observation has not been reported in healthy young adults and/or in response to a catabolic period of immobilisation.

A secondary rationale for β-lactoglobulin supplementation relates to the marked insulinotropic response and associated direct and/or indirect action of insulin on MPS. In this regard, the serum insulin AUC following β-lactoglobulin ingestion was 62% higher than casein and 30% higher than whey and corresponded with a higher plasma glucose-dependent insulinotropic peptide response [21]. In the presence of exogenous amino acids, insulin has been shown to stimulate MPS via the direct activation of mTORC1 signalling [6, 16, 24]. Insulin also stimulates endothelial-dependent vasodilation and microvascular recruitment [31] via activation of endothelial nitric oxide synthase (eNOS) [28], leading to an increased nutritive (insulin and amino acids) flow to skeletal muscle [15, 30]. Hence, via direct or indirect actions of insulin on MPS, the GIP-dependent insulinotropic properties of β-lactoglobulin serves as an alternative mechanism that may underpin the increased stimulation of MPS during a period of muscle disuse. Therefore, the objectives of this study are to:Establish whether combined β-lactoglobulin supplementation and resistance training for 1 week prior to 5 days of limb immobilisation will attenuate the decrease in integrated free-living rates of MPS during short-term muscle disuseEstablish whether combined β-lactoglobulin supplementation and resistance training for 1 week prior to 5 days of limb immobilisation will attenuate the decrease in leg lean mass, muscle fibre cross-sectional area and quadriceps muscle strength during short-term muscle disuse

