## Methods/design

### Experimental design

The aim of this study is to investigate the impact of a *complex* prehabilitation intervention that combines β-lactoglobulin supplementation with resistance exercise training on disuse-induced changes in MPS, leg lean mass, muscle thickness, muscle fibre cross-sectional area and quadriceps muscle strength in healthy, young adults. To address this aim, we will conduct a parallel, double-blind, 2-arm, randomised placebo-controlled trial. An overview of the trial design is displayed in Fig. 1 and detailed in chronological order under the ‘Experimental protocol’ section. The intervention group will combine a structured resistance exercise training programme with thrice daily dietary supplementation with 23 g of β-lactoglobulin. The placebo group will combine the same training programme with an energy-matched carbohydrate (dextrose) control. The study protocol will last 16 days. Day 1 will be a familiarisation session and days 2–4 will represent the ‘baseline’ period. Days 5–11 represent the ‘prehabilitation period’ whereby participants will combine resistance training with their assigned dietary supplementation regimen. Days 12–16 represent the muscle disuse induced ‘immobilisation period’ whereby participants will have their leg immobilised in a brace for 5 days and continue their assigned dietary supplementation regimen only (i.e. no resistance training). The primary endpoint of this study is the measurement of free-living, integrated rates of muscle myofibrillar protein synthesis (myo-MPS) that will be calculated at baseline, over the 7 day prehabilitation period and the 5 day immobilisation period separately. The trial will be parallel in design given that recruited participants must be tracer naïve for the valid determination of MPS rates. Secondary endpoints include measurements of leg lean mass, muscle thickness, muscle fibre cross-sectional area and quadriceps muscle strength that will be collected at baseline (i.e. prior to intervention), after prehabilitation (day 11) and following 5 days of immobilisation (day 16).

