#### Prehabilitation period

Days 4–11 will represent the ‘prehabilitation period’ and consist of a complex intervention that combines resistance exercise training with nutritional supplementation. The resistance training programme has been modified from the protocol described by Smeuninx et al. [27]. Participants will complete 4 sessions of bilateral resistance exercise training on leg press and leg extension machines during the prehabilitation period. The final bout of resistance exercise will be conducted ≥ 24 h prior to the 5 day immobilisation period. Each session will consist of two warm-up sets at 50% of 1RM, followed by six sets at 75% of their 1RM for both the single leg press and leg extension. Sets will consist of a target 12 repetitions and will be separated by 2 min rest. All training sessions will last ~ 30 min and will be conducted at a time convenient for the participant.

Participants also will receive a milk-based (β-lactoglobulin) or a carbohydrate supplement (dextrose monohydrate) 3 times per day over the prehabilitation and immobilisation periods. In total, the participant will consume 36 drinks over the 12-day period. Lacprodan® BLG-100 Acidic is a pure β-lactoglobulin derived from whey that delivers a unique amino acid profile and 4% more leucine compared to whey protein. The product is manufactured and packaged according to the relevant EU-regulations for food and food ingredients and/or FAO/ WHO Codex Alimentarius to ensure the milk/milk constituents used as raw material originate from healthy cows. The milk used in production is included in monitoring programmes for undesirable substances as required by regulations or HACCP-based risk assessment.

The placebo (dextrose monohydrate) will be modified to match the same flavour, colour and texture of β-lactoglobulin. The dextrose placebo will undergo the same microbiological testing as the β-lactoglobulin to ensure it is safe for consumption. The list of ingredients for dextrose is as follows: dextrose monohydrate, sucralose, citric acid anhydrous, pineapple flavouring (SC894020), lemon flavouring (SBD 213841) and colour (Yellow 410-WS-P). Both products will be stored at room temperature in a cool, dry place. Compliance will be monitored by requesting participants return all empty packaging.

On day 12, participants will undergo the same procedures (ultrasound, isokinetic dynamometry, and muscle biopsy) conducted at ‘Baseline’.

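### The objectives credit a combined supplement-and-training programme given before immobilisation, but the randomised comparison estimates only the effect of β-lactoglobulin versus dextrose, before and during immobilisation, in participants who all train

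*Protocol article*

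**What the plan says.** **What is claimed.** The two objectives at the end of the Background ask whether "combined β-lactoglobulin supplementation and resistance training for 1 week prior to 5 days of limb immobilisation will attenuate the decrease" in muscle protein synthesis (MPS) and, secondly, in lean mass, fibre size and strength. The gap to be filled, also in the Background, is the lack of studies of a "combined nutritional and exercise prehabilitation programme, implemented prior to a period of immobilisation". The aim under Experimental design is the impact of the complex intervention. The Abstract's Discussion says the study "will establish the impact of a bimodal prehabilitation strategy that combines" the two components, and the main Discussion states its hypothesis about the same combined intervention.

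**What is randomised.** Experimental design describes a "parallel, double-blind, 2-arm, randomised placebo-controlled trial". Of the active arm it says: "The intervention group will combine a structured resistance exercise training programme with thrice daily dietary supplementation with 23 g of β-lactoglobulin". Of the control arm: "The placebo group will combine the same training programme with an energy-matched carbohydrate (dextrose) control". During days 12–16 participants "continue their assigned dietary supplementation regimen only (i.e. no resistance training"). The Prehabilitation period section confirms that the drinks are taken "3 times per day over the prehabilitation and immobilisation periods", 36 drinks over 12 days, and that the training is bilateral. The Statistical analysis strategy has one between-group factor, β-lactoglobulin versus placebo.

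**The concern.** The objectives name the combination as the thing under test and place it in the week before immobilisation. The arms do not differ in training, and they differ in supplement after that week as well as during it. A reader who takes the objectives at face value could draw two conclusions that the comparison does not support:

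- A difference between arms could be read as proof that the combined programme works, and no difference as proof that it does not. If training alone protected both arms, the trial would be null although the package was effective.
- A difference during immobilisation could be credited to prehabilitation, when some or all of it might come from protein taken while the leg was braced.

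The Abstract looks ahead to patients awaiting hip or knee replacement. For them, advice to train and supplement beforehand is a different message from advice to take protein while immobilised.

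**Working it through.** **Inputs.** Prehabilitation is days 5–11 (7 days) and immobilisation days 12–16 (5 days), both from Experimental design. There are 3 drinks a day and 36 in total (Prehabilitation period). Training is the same in both arms (Experimental design). Biopsies are taken after an overnight fast on day 12, before the brace is fitted, and on day 16 (Immobilisation period; Muscle biopsies).

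**Step 1: reproduce the stated exposure.** 7 × 3 = 21 drinks before and 5 × 3 = 15 during immobilisation; 21 + 15 = 36, as stated. (The Prehabilitation period section also gives days 4–11; that would be 8 × 3 + 15 = 39, so the count fits days 5–11.)

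**Step 2: write down the contrast.** Let μ(t, a, b) be the mean outcome in immobilisation, with t = 1 for trained and 0 for untrained, a the drink before immobilisation and b the drink during it (B for β-lactoglobulin, D for dextrose). The trial observes two cells, μ(1,B,B) and μ(1,D,D). The randomised contrast is

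μ(1,B,B) − μ(1,D,D).

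**Step 3: compare with the programme effect.** Taking an untrained dextrose group as the no-programme reference,

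μ(1,B,B) − μ(0,D,D) = [μ(1,B,B) − μ(1,D,D)] + [μ(1,D,D) − μ(0,D,D)].

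The first bracket is what the trial estimates. The second is the effect of training, and no arm supplies μ(0,D,D). If the first bracket is zero and the second is positive, the programme works and the trial is null. An untrained reference without any drink would be equally unobserved.

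**Step 4: split the timing.**

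μ(1,B,B) − μ(1,D,D) = [μ(1,B,D) − μ(1,D,D)] + [μ(1,B,B) − μ(1,B,D)].

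The brackets are prior and concurrent supplementation. No arm stops the supplement when the brace goes on, so μ(1,B,D) is not observed and the two cannot be separated.

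**Step 5: look for another source of information.**

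- The non-immobilised leg is the within-subject control, but training is bilateral and supplementation is systemic. That leg is trained and supplemented too; it isolates immobilisation, not the programme.
- Within-arm change from baseline has no untrained or unsupplemented comparator.
- The planned between-group comparison of the change from baseline to prehabilitation does help. The second biopsy precedes the brace, so this comparison isolates the supplement's effect, given training, before disuse. It does not show carry-over into disuse.

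**The case against.** The strongest defence is that nothing is hidden. The Methods say plainly that the placebo arm trains, the Statistical analysis strategy names the factor, and the Background's rationale is that amino acids add to the response to exercise alone. A careful reader can recover the estimand as training plus β-lactoglobulin against training plus placebo, which is a legitimate add-on comparison. The objectives' timing phrase can also be read as describing the one week in which both components coincide. The Discussion calls the work proof-of-concept. It also cites a study in which 7 days of resistance prehabilitation alone did not attenuate the decline in myofibrillar MPS, which makes the scenario of training protecting both arms less likely.

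Much of this stands, and it limits the seriousness of the point. It does not remove it. The objectives name no comparator and omit the continued supplementation, and the anticipated conclusion concerns the bimodal strategy itself. The cited study was in older men under bedrest and cannot replace a concurrent untrained arm.

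Three stronger readings might be inferred and are not supported:

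- *The protein-free comparator defeats the objectives because it cannot test properties specific to β-lactoglobulin.* The objectives claim no superiority over other proteins. Those properties are offered as the reason for choosing the product, and a placebo comparator is a legitimate choice.
- *15/36 = 42% measures the bias.* It is a share of the schedule and measures no bias. If the day-16 drinks follow the fasted biopsy that day, which is an assumption, 4 × 3 = 12 drinks fall between the day-12 and day-16 biopsies, or 12/36 = 33%.
- *The trial says nothing about supplementation before disuse.* The baseline-to-prehabilitation comparison does.

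**Conclusion.** The point holds as a mismatch between the stated objectives and the randomised contrast. The trial can conclude on β-lactoglobulin versus energy-matched dextrose, taken before and during 5 days of immobilisation, in healthy young adults who all did the same training. It cannot conclude on the combined programme against no programme, and it cannot divide an arm difference during immobilisation between prior and concurrent supplementation.

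The size is one of interpretation; there is no numerical error to report. Randomisation, sample size, endpoints and analysis model are untouched by this point, and it introduces no bias into the between-arm test. It would be wrong to infer that the design is invalid: as an add-on trial it is defensible and openly described. The wording should be corrected, but the point does not threaten the trial.

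The conclusion rests only on design facts that the article states consistently: identical training in both arms, bilateral training, and supplementation continuing through immobilisation.

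**What to change.** Restate the aim, both objectives, the hypothesis and the anticipated conclusion as the contrast that is randomised. For example: *to estimate the effect of β-lactoglobulin compared with energy-matched dextrose, each taken through a 7-day training period and the following 5 days of single-leg immobilisation, on integrated MPS during immobilisation in healthy young adults who all complete the same training.* The second objective would follow the same form for its own outcomes.

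In addition:

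- Name the comparator (same training plus dextrose) and the continued supplementation wherever the intervention's effect is claimed, including the Abstract.
- Present the baseline-to-prehabilitation comparison as the one that isolates the supplement before disuse, and say that the immobilisation comparison reflects prior and concurrent supplementation together.
- Label any statement about the programme as a whole as uncontrolled within-arm description, and drop the claim that the trial establishes its impact.

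The cost is rewording and a narrower claim. No change to arms, sample size, procedures or analysis is needed. Answering the objectives as now worded would need a different comparator, which is a different trial.

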## Methods/design

### Experimental design

The aim of this study is to investigate the impact of a *complex* prehabilitation intervention that combines β-lactoglobulin supplementation with resistance exercise training on disuse-induced changes in MPS, leg lean mass, muscle thickness, muscle fibre cross-sectional area and quadriceps muscle strength in healthy, young adults. To address this aim, we will conduct a parallel, double-blind, 2-arm, randomised placebo-controlled trial. An overview of the trial design is displayed in Fig. 1 and detailed in chronological order under the ‘Experimental protocol’ section. The intervention group will combine a structured resistance exercise training programme with thrice daily dietary supplementation with 23 g of β-lactoglobulin. The placebo group will combine the same training programme with an energy-matched carbohydrate (dextrose) control. The study protocol will last 16 days. Day 1 will be a familiarisation session and days 2–4 will represent the ‘baseline’ period. Days 5–11 represent the ‘prehabilitation period’ whereby participants will combine resistance training with their assigned dietary supplementation regimen. Days 12–16 represent the muscle disuse induced ‘immobilisation period’ whereby participants will have their leg immobilised in a brace for 5 days and continue their assigned dietary supplementation regimen only (i.e. no resistance training). The primary endpoint of this study is the measurement of free-living, integrated rates of muscle myofibrillar protein synthesis (myo-MPS) that will be calculated at baseline, over the 7 day prehabilitation period and the 5 day immobilisation period separately. The trial will be parallel in design given that recruited participants must be tracer naïve for the valid determination of MPS rates. Secondary endpoints include measurements of leg lean mass, muscle thickness, muscle fibre cross-sectional area and quadriceps muscle strength that will be collected at baseline (i.e. prior to intervention), after prehabilitation (day 11) and following 5 days of immobilisation (day 16).

